## Abstract

**Background:**

Cardiac disease is the most common cause of morbidity and mortality in the United Kingdom. Even minor changes in thyroid hormone concentration may impact adversely on the cardiovascular system. Subclinical hypothyroidism (SCH) after admission for an acute cardiac problem has been associated with an increase in cardiac mortality and overall death. We have designed protocols for a prospective observational study to assess the association of thyroid function at the time of acute myocardial infarction (AMI) with cardiovascular outcomes, and a double-blinded randomised placebo-controlled trial of levothyroxine to evaluate its effect on LV function and vascular health.

**Methods/Design:**

ThyrAMI 1: This will be a prospective longitudinal observational study of patients with AMI that will be followed for 24 months to study the association between thyroid status at the time of AMI (within 24 hours of diagnosis) with vascular outcomes.

ThyrAMI 2: This will be a prospective double-blinded randomised placebo-controlled trial of levothyroxine of 12 months duration in patients with AMI and SCH.

Setting: Patients will be recruited from five hospitals in the North East of England.

Participants: One hundred patients with thyroid function tests within the subclinical hypothyroid range upon admission with an AMI and no previous history of thyroid disease.

Intervention: Levothyroxine will be administered at a starting dose of 25 mcg once daily, which will be increased at intervals if needed to maintain a TSH level between 0.4 to 2.5 mU/L, versus a placebo.

Randomisation: Participants will be randomized with a computerised randomisation algorithm, stratified by type of MI (NSTEMI versus STEMI), in a 1:1 ratio to levothyroxine therapy or placebo (as container or bottle numbers), starting within 21 (+/− 7) days of AMI.

Blinding: Assignment to either the LT4 or placebo arm will be double-blinded.

Outcomes: The outcome will be the effect of levothyroxine on ventricular function, endothelial function and blood coagulability and rheology.

**Discussion:**

There is evidence to suggest that treatment of SCH can improve cardiovascular parameters. Therefore, ThyrAMI 1 and ThyrAMI 2 will be the first trials investigating SCH in AMI to give a better insight into whether thyroid hormone levels are a key target for improving cardiovascular outcomes.

**Trial registration:**

ISRCTN number: ISRCTN52505169. Date of registration: 09/01/2015

## Background

Cardiac disease is the most common cause of morbidity and mortality in the United Kingdom, costing £29 billion [1]. Much research on cardiovascular disease has focused on men, as these diseases occur at younger ages and are more severe in males, and risk factors for cardiovascular disease in women are relatively understudied. Thyroid disease is predominantly a disease of women and is increasingly being recognised as an adverse cardiac risk factor. Levothyroxine is cheap (costs 5 pence/day), safe and commonly used generic drug (prescribed to 3% of the UK population). The appropriate use of levothyroxine in SCH patients with and without heart disease has the potential to optimise management of hypothyroidism to minimise vascular risk and to improve outcomes of AMI. The myocardium and vascular endothelial tissues have receptors for thyroid hormones and are sensitive to changes in circulating thyroid hormone concentration [2]. Even minor changes in thyroid hormone concentration may impact adversely on the cardiovascular system. Importantly, both mild hypothyroidism (SCH) and hyperthyroidism have been associated with a 20 to 80% increase in vascular morbidity and mortality risk [3-7]. This has huge population significance as a vascular risk factor, since at least 10% of older women have SCH, but this is under-recognised, owing possibly to a lack of commercial exploitability. Small intervention trials of levothyroxine in SCH have shown improvement in left ventricular function, vascular endothelial function and atherogenic lipid particles [8]. SCH after an acute cardiac problem has been associated with an up to 3.6-fold increase in cardiac mortality and a 2.3-fold increase in overall death [9,10]. Following experimental coronary artery ligation in an animal model of AMI, heart failure is associated with reduced thyroid hormone receptor expression in the myocardium, leading to tissue hypothyroidism [11]. Moreover, thyroid hormone administration improves cardiac contractility, left ventricular (LV) function, and augments myocardial remodelling [12]. In addition, thyroid hormone regulates angiogenesis, cardio-protection, cardiac metabolism, and myocyte regeneration at a molecular level, changes that can reverse left ventricular remodelling by favourably improving myocyte shape and geometry of LV cavity, thus improving recovery from AMI [13].

Analysis of more than 3,000 participants aged 65 years or older without heart failure at baseline, who were followed up for 12 years in the Cardiovascular Health Study, showed that SCH participants who were treated with levothyroxine had a 72% reduction in heart failure events [14]. Several other studies have shown similar results [15-17]. Thus, even mild hypothyroidism following AMI could be an important marker for poor outcome, and one that is ripe for cost-effective intervention if level 1 evidence of efficacy can be shown. In a recent preliminary analysis, we have shown that thrombus area, as measured by a model that simulates *ex vivo* coronary artery blood flow, is higher in people with SCH 7 to 10 days post non-ST elevation AMI despite dual anti-platelet therapy (with aspirin and clopidogrel) [18]. In multivariate analysis, serum TSH concentrations were directly associated with thrombus area, with a strength of association similar to other established cardiac risk factors such as diabetes mellitus and hypertension [18]. It is currently unknown whether levothyroxine treatment in SCH patients after an AMI can improve ventricular function, improve endothelial function and improve blood coagulability and rheology. Therefore, this project aims to provide level 1 evidence to answer these important questions. This programme has two separate yet interlinked studies: ThyrAMI 1 - an observational longitudinal study to assess association of thyroid function at the time of AMI with cardiovascular outcomes, and ThyrAMI 2 - a randomised placebo-controlled interventional study of levothyroxine in SCH patients to evaluate effect on LV function and vascular health.

## Methods/Design

### ThyrAMI 1

#### Aim

The aim of this trial is to assess what proportion of individuals with AMI have thyroid dysfunction and whether thyroid function at the time of AMI is related to adverse vascular outcomes.

### Study design

The study is designed as a prospective longitudinal observational study of unselected patients with AMI who will be followed for 24 months (Figure 1).

**Figure 1 Fig1:**
[figure not shown]
**Flow chart representing ThyrAMI 1 observational study and identification of potential cohort for the interventional trial ThyrAMI 2.**

### Primary objectives

The primary objective is to assess the association between thyroid status at the time of AMI (within 24 hours of diagnosis) with vascular outcomes (another AMI, coronary revascularisation or death due to ischaemic heart disease) over 24 months.

### Secondary objectives

The secondary objectives are as follows:The proportion of individuals with thyroid dysfunction at the time of AMI (overt hypo- and hyperthyroidism, subclinical hypo- and hyperthyroidism, and isolated low FT3)Association between thyroid function at the time of AMI with markers of severity of AMI (troponin, LV function, and coronary artery disease on angiogram).Relation between thyroid function at the time of AMI with all-cause mortality over 24 months.Association between thyroid function at the time of AMI with new diagnoses of heart failure, atrial fibrillation or stroke.

### Participant population

The study population are patients post-AMI in five different hospitals in the North East of England.

Inclusion criteria are as follows:Adult males and females (aged 18 years or older).Acute myocardial infarction diagnosed in the preceding 24 hours (defined as chest pain with dynamic ECG changes or increased troponin enzymes (at least a fourfold increase above the local laboratory reference range).Participants in other research studies will be eligible for inclusion as this is an observational study.

Exclusion criteria are as follows:Patients who are unable to provide informed consent.Those with advanced malignancy (who are unlikely to survive for more than 6 months in the opinion of local investigator).Those on medications that can affect thyroid function such as amiodarone, lithium, carbimazole and propylthiouracil. Patients on levothyroxine will be included, but their results will be analysed separately.

### Screening, recruitment and consent

#### Identification, screening and recruitment of participants

Eligible participants will be identified from acute hospitals. All individuals that fit the study criteria will be approached and provided with a participant information sheet for ThyrAMI 1, and informed consent will be obtained. They will have their thyroid function checked, and a case record form will be completed. Patients that are otherwise eligible to be included but have been discharged and have not had their thyroid function checked will be approached via telephone, and initial consent will be obtained prior to requesting these tests be done on the stored serum, if still available in the Laboratory. A screening log will be kept at each site with a unique identifier for each participant who is approached for the study. Recruitment will take place over a period of 12 months in all participating centres See Figure 1.

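### ThyrAMI 1's telephone route after discharge sets no draw time for the stored serum and admits only patients alive at the call, while the outcomes include death over 24 months

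*Protocol article*

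**What the plan says.** All references are to the ThyrAMI 1 part of the protocol article.

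- **Study design:** a "prospective longitudinal observational study of unselected patients with AMI who will be followed for 24 months".
- **Primary objectives:** the association of "thyroid status at the time of AMI (within 24 hours of diagnosis) with vascular outcomes". The outcomes are reinfarction, coronary revascularisation and death from ischaemic heart disease over 24 months.
- **Secondary objectives:** these include the proportion with thyroid dysfunction at the time of the infarction, and "Relation between thyroid function at the time of AMI with all-cause mortality over 24 months".
- **Participant population:** "Acute myocardial infarction diagnosed in the preceding 24 hours" is an inclusion criterion.
- **Identification, screening and recruitment of participants:** beside the in-hospital approach, otherwise eligible patients who "have been discharged and have not had their thyroid function checked will be approached via telephone". After initial consent, the tests are requested on stored serum if the laboratory still holds it. No draw time is required and no limit is set on the delay to the call.
- **Data analysis:** chi-squared tests and t-tests for binary outcomes, and Cox models for time to event. No time origin is given. Levothyroxine users are to be analysed separately (Participant population); nothing similar is said about enrolment route.

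**The concern.** Two things do not fit together.

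**Timing.** A discharged patient will ordinarily be more than 24 hours past diagnosis when consent is given, so the inclusion criterion cannot be met at enrolment as it is worded. Nor does anything tie the stored serum to the 24-hour exposure window. Timing matters by the protocol's own logic: ThyrAMI 2 accepts subclinical hypothyroidism only if it is present on the day of admission and again 7 to 10 days after the infarction, so one TSH value is not treated as fixed over those days. A later in-hospital sample would measure a different exposure.

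**Survival to enrolment.** A telephone-route patient has survived both the admission and the interval to the call. A comparable untested patient who died before the call can never enter. This is left truncation in a study of "prospective longitudinal observational study of unselected patients with AMI" that counts cardiac and all-cause deaths. The chi-squared and t-tests take no account of when a participant came under observation. Mortality would be understated, prevalence estimated partly in survivors, and the thyroid association possibly distorted.

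**Working it through.** The article gives no sample size, event count or expected mortality for ThyrAMI 1, so there is no stated figure to reproduce. The timing part follows from the sections set out above. The survival part can only be illustrated.

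**Formula.** Let r be the true 24-month death risk, d the risk of dying before a call could be made, and f the share of the source population reachable only by telephone. Of that share, those who die early never enter, so

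observed risk = (r − f·d) / (1 − f·d).

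**Inputs.**
- From the Background section: relative risks of 2.3 (overall death) and up to 3.6 (cardiac mortality).
- Assumed: reference-group r = 5% or 10%; early share of deaths e = 0.2 or 0.5, so d = e·r; f = 0.1, 0.3 or 0.5.

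**1. Absolute risk in the reference group.**
- r = 10%, e = 0.2, f = 0.1: (0.10 − 0.002)/(1 − 0.002) = 9.8%.
- r = 10%, e = 0.5, f = 0.5: (0.10 − 0.025)/(1 − 0.025) = 7.7%.
- r = 5%: from 4.9% (e = 0.2, f = 0.1) down to 0.0375/0.9875 = 3.8% (e = 0.5, f = 0.5).

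The relative shortfall runs from about 2% to 24%.

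**2. Relative risk, same f and e in both thyroid groups.** With r = 10%, e = 0.5, f = 0.5 and a true ratio of 2.3, the exposed risk is (0.23 − 0.0575)/(1 − 0.0575) = 18.3%, and 18.3/7.69 = 2.38. Over the whole grid, 2.3 becomes 2.30 to 2.38 and 3.6 becomes 3.61 to 3.86. The ratio hardly moves and, if anything, rises.

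**3. Relative risk, only one thyroid group reached by telephone (extreme case).** With r = 5%, e = 0.5, f = 0.5 and a true ratio of 2.3:
- Exposed group only: (0.115 − 0.02875)/(1 − 0.02875) = 8.88%, and 8.88/5 = 1.78.
- Reference group only: 11.5/3.80 = 3.03.

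For a true ratio of 3.6 the corresponding values are 2.83 and 4.74.

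**4. Relative risk, excess concentrated in early death.** Assume the reference group has 4% early deaths and 8% later deaths among survivors, with ratios of 3.6 early and 1.3 later.
- Reference r = 0.04 + 0.96 × 0.08 = 0.117.
- Exposed r = 0.144 + 0.856 × 0.104 = 0.233. True ratio 2.0.
- f = 0.3: exposed (0.233 − 0.0432)/(1 − 0.0432) = 0.198; reference (0.1168 − 0.012)/(1 − 0.012) = 0.106; ratio 1.87.
- f = 0.5: exposed 0.161/0.928 = 0.174; reference 0.0968/0.98 = 0.0988; ratio 1.76.

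If 30% and 50% are read instead as shares of enrolled patients, the ratios are 1.84 and 1.71. In this case the association is diluted, but only because the excess was placed early by assumption.

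**The case against.** The best defence is that the route catches patients missed in hospital and is limited to those who were otherwise eligible, which suggests that the 24-hour criterion had been met during the admission. Serum stored from that admission may well be the admission sample, and late consent does not mean late exposure. Time origin, delayed entry and sensitivity analyses by route are commonly left to a full protocol or analysis plan that is not shown. Any cohort that needs consent loses deaths before consent. The patients are untested when called, so their thyroid status cannot steer who is called.

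Much of this stands. A reader might infer that the route contradicts the 24-hour exposure definition. The documents do not support that: they allow a late sample without saying that one will be used. The absence of a time origin is not a fault in itself, and that the routes are pooled with time running from the infarction is an inference.

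The defence does not remove the gap in the recruitment wording, or the conflict with the enrolment window as written. Nor can a later analysis plan repair the chi-squared and t-tests that are named, since they ignore entry time. Counting from consent would remove the death-free period, but the telephone-route group would still consist of survivors, observed over a later window. Unknown status at the call makes a one-sided telephone share less likely, but length of stay or availability of serum could still differ with thyroid status.

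**Conclusion.** The point holds in a limited form and is worth correcting. The enrolment window, the exposure window and the telephone route are not aligned, and the stored serum has no required draw time. If time is counted from the infarction, telephone-route patients contribute a period in which death is impossible, and observed 24-month mortality is too low.

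The size is unknown. The 2% to 24% shortfall rests wholly on assumed mortality, early-death share and telephone share, and a 50% telephone share has no support in the article.

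Two stronger readings are tempting and should not be drawn:

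- **That the period before the call is free of events.** Only death is excluded. A reinfarction or revascularisation before the call could still be recorded, so the primary composite is affected less than all-cause mortality.
- **That the thyroid association is diluted.** With equal telephone and early-death shares the ratio is nearly unchanged; with unequal shares it can move either way. The 3.6-fold figure is an upper value for cardiac mortality and is not described as an early effect, and the later ratio of 1.3 is an assumption.

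**What to change.** 1. Reconcile Primary objectives, Participant population and the recruitment section: state that the 24-hour criterion applies to diagnosis and blood draw, and accept stored serum only if it was drawn within 24 hours of diagnosis.
2. Record enrolment route and consent date for every participant.
3. In the Cox model, let each participant enter the risk set at consent (delayed entry). Make this the main analysis of outcomes that include death, in place of the chi-squared and t-tests on binary outcomes.
4. Report the 24-month proportions and the prevalence estimate with and without telephone-route patients, as a sensitivity analysis only. Restricting the main estimates to patients enrolled within 24 hours would drop those discharged before they were approached, which is a selection of its own.

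The cost is protocol wording, two data fields and a standard model option. Telephone-route patients without an early sample are lost. In a delayed-entry analysis of time to first event, non-fatal events before consent do not count, and the method assumes that the time of entry is unrelated to later risk given the covariates.

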### Consent procedures

All informed consent discussions will be undertaken by experienced research staff (per delegation log) involved in the study with an opportunity for participants to ask any questions. Following receipt of information about the study (that is, provision of the study invitation pack), participants will be given reasonable time to decide whether or not they would like to participate. Those wishing to take part will provide written informed consent by signing and dating the study consent form and initialling relevant sections, which will be witnessed and dated by a member of the research team with documented, delegated responsibility to do so. Participants for ThyrAMI 1 will be informed via the Participant Information Sheet that they may be approached to consider participating in ThyrAMI 2 if their thyroid blood tests are in the inclusion range.

The original signed consent form will be retained in the Investigator Site File, with a copy in the relevant clinical notes and a copy provided to the participant. The participant will specifically consent to their GP being informed of their participation in the study. The right to refuse to participate without giving reasons will be respected.

The information sheet and consent form for the study will be available only in English. Interpreters will be arranged for all visits of participants who require them either for verbal translation or for deaf participants wishing to take part in the study, via local NHS arrangements. Qualified interpreters will be used to explain the consent form and information sheet, and great priority will be placed on finding the most direct communication.

### Data analysis

The relationship between the outcomes and thyroid status categories (euthyroid, subclinical hypothyroid, subclinical hyperthyroid and isolated low FT3) will be examined. A chi-squared test will be used to investigate the association between categorical measures of thyroid status and categorical and/or binary measures of CV outcome. Independent sample t-tests will be used to investigate the association between continuous measures of thyroid function (TSH, FT4 and FT3) and binary measures of CV outcome. Cox regression models will be used to explore the association between continuous and categorical measures of CV with survival (time to event).

### ThyrAMI 2

#### Objective

To determine whether treatment of SCH with levothyroxine following AMI improves left ventricular function, thrombus area, endothelial function, health status, quality of life and is safe.

### Study design

This study is a prospective randomised placebo-controlled trial of levothyroxine of 12 months duration in patients with subclinical hypothyroidism (serum TSH persistently 4.01 to 10.0 mU/l, normal FT4) starting within 21 days following AMI. The day of AMI is the date of diagnosis or the date of admission to hospital, whichever is later.

### Primary outcome measure

The primary outcome measure will be change in LV ejection fraction as assessed by magnetic resonance imaging. Cardiac magnetic resonance (MR) is considered the gold standard for evaluating cardiac volumes and function [19]. Gradient echo sequences provide a naturally high level of contrast between intracavitary blood and myocardium, thus allowing an accurate and reproducible determination of LV volumes, mass and calculation of stroke volume and ejection fraction. In this context, additional information can also be drawn from application of the more recent cardiac MR tagging analysis, which represents a noninvasive highly accurate method for direct quantification of regional systolic function [20]. Cardiac MR imaging will be performed in the dedicated 3 T MRI centre at Newcastle University.

### Secondary outcome measures

Secondary outcome measures will include the following:Left ventricular systolic and end diastolic volumes and myocardial viability: Cardiac MR parameters of both global and segmental LV function measurements will be obtained as per standardised protocols already in place in the Newcastle MR centre using a steady state free precession or fast gradient echo technique. In addition, further scans will be obtained 15 to 20 minutes after intravenous gadolinium-chelate administration (delayed enhancement MRI). Regions of nonviable myocardial tissue will be identified as areas of increased enhancement (hyper enhancement) whereas viable tissue will have null (black) on the acquired images.Thrombus burden: The Badimon chamber is a highly reproducible clinical *ex vivo* model of thrombosis that mimics flow conditions within the coronary circulation of man [21]. The device incorporates two chambers with internal flow channels of different diameters, one simulating high-shear flow of 1690 ml/s and the other simulating low-shear flow. The internal flow channels are lined with porcine aortic tunica media - the thrombogenic substrate. After perfusion with venous blood from the patient, flowing at 10 mL min −1 for 5 min, aortic segments are fixed in 10% formalin for 72 h. Total thrombus burden is measured using validated computer-assisted planimetry using IMAGE-PRO PLUS software (Media Cybernetics, Inc., Bethesda, MD, USA). The results are the mean of the analysed sections (μm2 .mm-1). The measurements will be performed at the Clinical Research Facility (CRF), where there are professionals who have considerable experience using this technique in other high vascular risk groups.Thromboelastography (TEG™): This is a noninvasive measure for evaluating efficiency and quality of *ex vivo* thrombus formation. Quantitative measures include clotting time parameters, clot strength and clot lysis. These parameters have been validated as highly correlated with longer term cardiac outcomes in several conditions of risk [22,23]. TEG™ will be measured at the CRF, RVI, Newcastle.Endothelial function: Endothelial dysfunction is the earliest stage in the atherosclerosis disease process. In this study, endothelial function will be assessed by measuring peripheral arterial tone using a validated tool, EndoPAT™ [24]. Endothelial function assessment using the EndoPAT™ has been shown to have a high degree of correlation with coronary artery endothelial function [25], the severity and extent of coronary artery disease [26], and traditional cardiovascular risk factors [27] and is useful in predicting future cardiovascular events [28]. EndoPAT™ assessments will be performed at the Clinical Research Facility, RVI, Newcastle at baseline and at the end of the study.Platelet reactivity: The reactivity (inhibition) of platelets to anti-platelet agents such as aspirin, clopidogrel, prasugrel and ticagrelor will be quantified by the point-of-care monitor VerifyNow™ (Accumetrics, CA, USA). Arachidonic acid reactive units and P2Y12 reactive units will be recorded at baseline and at the end of the study. This test will not be carried out in individuals who take anticoagulants such as warfarin.Safety assessments: The safety of levothyroxine therapy in post-AMI patients will be assessed at each study visit by enquiry of symptoms by New York Heart Assessment (NYHA) category classification, ECG recording for rhythm disturbance and peripheral oxygen levels by pulse oximetry (at rest).QoL and depression: This will be assessed by validated tool of measuring health status, the Short Form 12 four week recall (SF-12™), a disease specific questionnaire for heart failure, the Minnesota Living With Heart Failure Questionnaire™, and the Centre for Epidemiologic Studies Depression Scale (CES-D), at baseline and at the end of the study.
